## **5. Sample size estimation**

The sample size was estimated using a log-rank test based on a 3-year DFS with a noninferiority margin of 10%. At the time of this trial design, a noninferiority margin of 10% was determined to be clinically acceptable. Considering distinct prognoses in patients with stage I versus II/III disease, the sample size was calculated separately. Assumptions for 3-year DFS rate in the open surgery group were 94.3% and 75.2% for clinical stage I and II/III, respectively, 359 patients with stage I disease (laparoscopic 240, open 119), 609 patients with stage II/III disease (laparoscopic 406, open 203), and a total of 968 patients (laparoscopic 646, open 322) were required to provide an 80% power with a one-sided  $\alpha$  of 2.5%. One thousand sixty-five patients were aimed to enroll to allow for exclusions after randomization to maintain the required statistical power. All calculations allowed for a 20% dropout. The planned and follow-up period were three years and five years, respectively.

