## **8. Study endpoints**

### **8.1 Primary outcome measure**

3-year DFS rate (final calculation is done 3 years after the last participant is enrolled)

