## 8 Statistical analyses

### 8.1 Sample size estimation

The sample size was estimated using a log-rank test based on a 3-year DFS with a noninferiority margin of 10%. At the time of this trial design, a noninferiority margin of 10% was determined to be clinically acceptable. Considering distinct prognoses in patients with stage I versus II/III disease, the sample size was calculated separately. Assumptions for the 3-year DFS rate in the open surgery group were 94.3% and 75.2% for clinical stage I and II/III diseases, respectively, with 359 patients with stage I disease (laparoscopic 240, open 119), 609 patients with stage II/III disease (laparoscopic 406, open 203), and a total of 968 patients (laparoscopic 646, open 322) were required to provide an 80% power with a one-sided  $\alpha$  of 2.5%. One thousand sixty-five patients were aimed to enroll to allow for exclusions after

randomization to maintain the required statistical power. All calculations allowed for a 20% dropout. The planned and follow-up period were three years and five years, respectively.

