**Table 7. The DFS (mon) for Laparoscopic Surgery vs Open Surgery within 3 Years after Surgery (mITT)**

|                    | Laparoscopic Surgery Group | Open Surgery Group | P value |
|--------------------|-----------------------------------|---------------------------|-----------------------|
| N           | XXX                               | XXX                       | X.XXX                 |
| Censored(%) | XX(XX.X)                          | XX(XX.X)                  |                       |
| Events(%)   | XX(XX.X)                          | XX(XX.X)                  |                       |
| 25%(95%CI)  | XX.X (XX.X~XX.X)                  | XX.X (XX.X~XX.X)          |                       |
| 50%(95%CI)  | XX.X (XX.X~XX.X)                  | XX.X (XX.X~XX.X)          |                       |
| 75%(95%CI)  | XX.X (XX.X~XX.X)                  | XX.X (XX.X~XX.X)          |                       |

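### The stated 80% power per stage at one-sided 2.5% with 20% dropout is not delivered at the primary analysis three years after last enrolment; by log-rank it is about 70–75%

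*Combined protocol and SAP*

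**What the plan says.** Protocol section 5, the protocol summary and SAP 8.1 carry the same paragraph. The method is a log-rank test with a 10-point margin in 3-year DFS, calculated separately by stage group. The assumed rates in the "open surgery group were 94.3% and 75.2% for clinical stage I and II/III diseases, respectively". The resulting 359 stage I patients (240 laparoscopic, 119 open) and 609 stage II/III patients (406 and 203), 968 in all, "were required to provide an 80% power with a one-sided" alpha of 2.5%. The enrolment target is 1065, to cover exclusions after randomization. The paragraph closes with two further statements: "All calculations allowed for a 20% dropout", and "The planned and follow-up period were three years and five years, respectively".

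Elsewhere the plan sets different conditions for the analysis:

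- **Timing.** Protocol 8.1 and SAP 7.1 define the primary outcome as "3-year DFS rate (final calculation is done 3 years after the last participant is enrolled".
- **Window.** SAP Table 7 is titled "The DFS (mon) for Laparoscopic Surgery vs Open Surgery within 3 Years after Surgery (mITT"; Table 8 repeats this for the per-protocol set.
- **Alpha.** Protocol 12.2 and SAP 8.3.3 report the Cox hazard ratio with a one-sided 95% confidence interval, which is a one-sided 5% test.

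**The concern.** A log-rank power claim depends on the number of events, and so on how long patients are followed. The sample size paragraph gives five years of follow-up, but the primary analysis comes three years after last enrolment. It gives one-sided 2.5%, but the planned interval works at one-sided 5%. It says a 20% dropout is included without saying how. If these settings do not fit together, the stated 80% describes an analysis other than the planned one.

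What is at stake is the per-stage claim, since distinct prognosis is the plan's own reason for sizing the two stage groups separately. A reader who trusts 80% in each group would give too much weight to a stage II/III result that fails to exclude the margin.

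**Working it through.** **Inputs from the documents.** 3-year DFS 94.3% and 75.2%; margin 10 points; allocation 2:1; N = 359 and 609; 80% power; one-sided 2.5%; 20% dropout; analysis three years after last enrolment.

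**Assumptions.** DFS is exponential. The true hazard ratio is 1, because no DFS rate is given for the laparoscopic arm. The three-year planned period is read as uniform accrual over three years.

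**1. Margin as a hazard ratio.** ln(0.843)/ln(0.943) = 2.910 for stage I; ln(0.652)/ln(0.752) = 1.501 for stage II/III.

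**2. Events needed.** D = (1.960 + 0.842)² / [(2/3)(1/3)(ln HR)²] gives 31.0 and 214.4.

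**3. Probability of an event by the primary analysis.** The yearly hazard is λ = −ln(S)/3, that is 0.01956 and 0.09501. With three years of accrual and three more of follow-up, P = 1 − [e^(−3λ) − e^(−6λ)]/(3λ) = 0.0841 and 0.3457.

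**4. Attempt to reproduce 359 and 609.** N = D/P, divided by 0.8 where dropout is included:

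| Settings | Stage I | Stage II/III |
|---|---|---|
| 2.5%, 3+3 years, dropout as N/0.8 | 460 | 775 |
| 2.5%, 3 years accrual + 5 years, N/0.8 | 324 | 584 |
| 2.5%, 3+3 years, no dropout | 368 | 620 |
| 5%, 3+3 years, N/0.8 | 362 | 611 |
| 5%, Freedman-type formula, 3 years per patient, no dropout | 358 | 609 |

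The stated inputs with the three-year analysis (first row) do not give 359 and 609. Several other combinations come close.

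**5. Events expected.** No loss: 359 × 0.0841 = 30.2 and 609 × 0.3457 = 210.5. With 20% contributing nothing: 24.2 and 168.4. DFS cut at three years per patient, no loss: 359 × 0.057 = 20.5 and 609 × 0.248 = 151.0.

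**6. Power.** Φ(ln HR × √(D × 2/9) − z), with z = 1.960 for 2.5% and 1.645 for 5%:

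| Analysis | Loss | Stage I | Stage II/III |
|---|---|---|---|
| 3+3 years, 2.5% | none | 79.0% | 79.3% |
| 3+3 years, 2.5% | 20% lost outright | 69.7% | 70.0% |
| 3+3 years, 2.5% | exponential, 20% by 3 years | 72.2% | 72.9% |
| 3+3 years, 2.5% | exponential, 20% by 5 years | 74.9% | 75.5% |
| Cut at 3 years, 2.5% | none | 62.5% | 65.2% |
| Cut at 3 years, 2.5% | 20% lost outright | 53.1% | 55.7% |
| Cut at 3 years, 2.5% | exponential, 20% by 5 years | 59.7% | 62.5% |
| 3+5 years, 2.5% | 20% lost outright | 83.8% | 81.6% |
| 3+3 years, 5% | 20% lost outright | 79.7% | 79.9% |

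A 6,000-run simulation of the Cox upper limit (3+3 years, 2.5%) gave 73.9%/78.7% with no loss and 64.1%/69.0% with 20% lost outright. The formula is thus somewhat generous to stage I, where events are few.

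**7. The same margin as a difference in 3-year rates.** SE = √[S(1−S)(1/n_L + 1/n_O)], with arm sizes × 0.8 for loss: 0.0291 and 0.0415. Power = Φ(0.10/SE − 1.960) = 93% and 67%. With no loss it is 97% and 77%. In the simulation with gradual loss, the Kaplan–Meier difference at three years gave about 73% for stage II/III.

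**The case against.** The best defence is that the plan contains settings that do deliver the power. Five years of follow-up, as in the sample size paragraph, gives 84%/82% after a 20% loss. The one-sided 95% interval in the analysis sections gives about 80%/80% at the three-year analysis. Both points stand, and they make this a failure to reconcile sections more than a gross error. But the first is not the primary analysis, and the second is not the stated 2.5%.

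Three stronger readings are tempting but go beyond the documents.

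- **That 359 and 609 must have been computed at one-sided 5%.** The closest fits are there, but 2.5% with no dropout gives 368 and 620, within about 2.5% and 1.9%. The plan does not show which recipe was used.
- **That planned power is 53%.** That needs truncation at three years, which appears only in table titles. The methods text and the Cox table (SAP Table 9) set no such limit.
- **That 1065 is a failed 20% inflation.** The text assigns the extra patients to exclusions after randomization and mentions dropout separately, so this step says nothing about the 20%. Even if all 1065 were analysed (about 395 and 670), log-rank power at 3+3 years and 2.5% would be about 74–79% with 20% dropout.

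Nor does SAP 8.3.3 or its DFS tables plan a stage-specific noninferiority test, so the consequence is a misstated design claim and weak stage II/III inference, not a failed primary test.

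**Conclusion.** The point holds. At one-sided 2.5%, with the log-rank method and the stated primary analysis time, 80% with a 20% dropout allowance is not delivered in either stage group. Power is about 70–75%, and just under 80% even with no loss. If DFS is truncated at three years, it is about 53–63% with dropout.

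The stage I shortfall is specific to the hazard-ratio scale, where the margin is 2.91; on the 3-year rate-difference scale stage I is adequate. Stage II/III is short on both scales.

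The figures rest on uniform three-year accrual, exponential DFS and no true difference. The range reflects how the 20% loss is spread over time, which the plan does not state.

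**What to change.** In Protocol section 5, the protocol summary and SAP 8.1, with matching edits to Protocol 12.2 and SAP 8.3.3:

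1. Settle one alpha. To keep 2.5%, judge noninferiority on the upper limit of a two-sided 95% interval. If the one-sided 95% interval stays, say that the test is at one-sided 5%.
2. State the follow-up behind the power calculation (three or five years after last enrolment) and whether DFS is truncated at three years per patient; align the titles of SAP Tables 7 and 8.
3. State how the 20% dropout entered 359 and 609.
4. Restate per-stage power for that analysis: about 70–75% by log-rank at 2.5% with 20% dropout and no truncation. Alternatively, give the required events, 31 and about 214.

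The cost is rewording. No patients are added and the primary method is unchanged. If 2.5% and the three-year analysis are kept, the published per-stage power becomes less favourable.

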## **8.2 Analysis datasets**

**(1) Modified intention-to-treat (mITT):** The mITT population is defined as all randomized subjects except those excluded after randomization. The modified intention-to-treat (mITT) population will serve as the primary population for efficacy analyses in this study.

**(2) Per-protocol set (PPS):** The PPS includes patients who underwent the assigned surgery only. In other words, the participants who meet the trial plan, have good compliance, and complete the items specified in the eCRF are included in the per-protocol (PP) analysis. PP analysis is mainly applied to the primary outcome measure.

**(3) Safety set (SS):** The SS includes the actual data of participants who have received treatment and have records of safety indicators. The missing data of safety indicators cannot be obtained from carry-over from previous records. The dataset includes some patients excluded from the trial, e.g., those whose age exceeds the inclusion criteria. The incidence of adverse reactions is determined by using the number of cases in the SS as a denominator.

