### **12.1 Analysis datasets**

#### **● Modified Intention-to-treat (mITT)**

The mITT population is defined as all randomized subjects who received open surgery or laparoscopic surgery. The modified intention-to-treat (mITT) population will serve as the primary population for efficacy analyses in this study.

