### **12.2 Statistical methods**

#### **(1) Case enrollment analysis**

- The number of patients, the number of enrolled patients, and the number of patients who complete the trial in each center are listed to generate three analysis datasets (FAS, PPS, and SS).
- The patients who drop out and are excluded are listed, along with the reasons.

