## **5 Exclusion criteria**

1) Aged < 18 or > 75 years;

2) Concurrent or previous malignancies within five years;

3) Need for emergency surgery due to intestinal obstruction, intestinal perforation, intestinal hemorrhage, etc. ;

4) Previous history of colorectal surgery that might affect the reconstruction of the digestive tract;

5) Need to remove other organs in addition to the rectum;

6) ASA classification IV or V;

7) Current pregnancy or lactation:

- Women of childbearing age with a positive pregnancy test at baseline or who have not taken a pregnancy test; postmenopausal women must be at least 12 months postmenopausal;

- Sexually active men and women (of reproductive age) who are unwilling to take contraceptive measures during the study period;

8) Severe mental illness;

9) Inability to tolerate surgery due to severe emphysema, interstitial pneumonia, ischemic heart disease, etc.;

10) Continuous systemic steroid therapy within the last month;

11) Contraindications to laparoscopic surgery;

12) Patients and their family members cannot understand the conditions and objectives of this study.

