**Table 4. Surgical Details**

| Characteristics                        | Laparoscopic Surgery Group
(n=XXX) | Open Surgery Group
(n=XXX) | P value |
|-----------------------------------------------|-----------------------------------------------|---------------------------------------|----------------|
| Conversion to open resection, n (%)    | XXX(XX.X)                                     | -                                     | -              |
| Operative time, median (IQR), min      | XX (XX.X–XX.X)                                | XX (XX.X–XX.X)                        | X.XXX          |
| Combined resection, n (%)              | XXX(XX.X)                                     | XXX(XX.X)                             |                |
| Uterus                                        | X                                             | X                                     |                |
| Ovaries                                       | X                                             | X                                     |                |
| Seminal vesicle                               | X                                             | X                                     |                |
| Vagina                                        | X                                             | X                                     |                |
| Bladder                                       | X                                             | X                                     |                |
| ...                                           | X                                             | X                                     |                |
| ...                                           | X                                             | X                                     |                |
| ...                                           | X                                             | X                                     |                |
| Estimated blood loss, median (IQR), mL | XX (XX.X–XX.X)                                | XX (XX.X–XX.X)                        | X.XXX          |
| Intraoperative complications No. (%)   | XXX(XX.X)                                     | XXX(XX.X)                             | X.XXX          |

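### The SAP's primary analysis set rests on an exclusion rule that is never stated, and it differs from the protocol's set of the same name

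*Combined protocol and SAP*

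**What the plan says.** Both documents make mITT the primary efficacy set; SAP 8.2(1) puts it as "The modified intention-to-treat (mITT) population will serve as the primary population for efficacy analyses in this study". They define it differently.

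- SAP 8.2(1): "The mITT population is defined as all randomized subjects except those excluded after randomization".
- Protocol 12.1: "The mITT population is defined as all randomized subjects who received open surgery or laparoscopic surgery".

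SAP 8.2(3), on the safety set, shows that a treated patient can be out of the trial: "The dataset includes some patients excluded from the trial, e.g., those whose age exceeds the inclusion criteria". SAP 8.1 expects removals: "One thousand sixty-five patients were aimed to enroll to allow for exclusions after" randomization, against a requirement of 968. SAP 8.3.1 and SAP Table 2 call for a listing of excluded cases with reasons. Protocol 12.2(1) still uses another label, in the words "to generate three analysis datasets (FAS, PPS, and SS"; the matching line in SAP 8.3.1 names mITT instead.

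Three other places bear on the point. Protocol 11.1.9 states that the trial is open-label. Protocol section 12 says the statistical plan is settled before database lock in light of the data. Protocol 8.4.1 starts DFS at surgery, whereas 8.4.2 starts OS at randomization.

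**The concern.** The SAP rule is circular: a patient is out of the set because he or she was excluded, and exclusion is defined nowhere. Two statisticians given the same database could not be sure of deriving the same primary population from it. The protocol rule can be applied, but it gives a different population.

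The denominator of a noninferiority claim is therefore open. Staff and analysts can know the arm, no blinded review of exclusions is described, and the DFS table shells (SAP Tables 7 to 9) cover only mITT and PPS. No all-randomized analysis is planned to show whether the removals mattered; ITT appears only in the SAP's abbreviation list. If poor-prognosis patients were removed more often from the laparoscopic arm than from the open arm, the result would move towards noninferiority. The reverse imbalance would move it away.

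**Working it through.** **1. Do the two rules give the same set?** They would coincide only if every excluded patient had no operation and every non-operated patient was excluded.

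| Patient, after randomization | Protocol 12.1 | SAP 8.2(1) |
|---|---|---|
| Over-age, operated on, then excluded from the trial | in | out |
| Withdraws before any operation | out | not determined |
| Operated on, not excluded | in | in |

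The first row is the SAP's own example from 8.2(3), so the sets differ.

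**2. The plan's own figures.** 359 + 609 = 968 and 646 + 322 = 968. The enrolment target is matched by 968 × 1.10 = 1064.8, rounded up to 1065; the 10% is inferred, not stated. The allowance is 1065 − 968 = 97, and 97/1065 = 9.1%, over both arms. The 968 itself is reproduced only approximately. A log-rank calculation with HR = ln(p − 0.10)/ln(p), which is 2.91 for stage I and 1.50 for stage II/III, needs 31 and 215 events. With 3 years of accrual, 3 years of follow-up and no dropout inflation, this gives 368 and 622 patients, within 3% of 359 and 609. The present point does not depend on which variant was used.

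**3. How far could one-sided removals move DFS?** Inputs from the documents: open-arm 3-year DFS of 94.3% and 75.2%, the stratum sizes, and the 10-point margin. Pooled rate: (359 × 0.943 + 609 × 0.752)/968 = 82.3%. At the margin: 82.3 − 10 = 72.3%.

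Assumptions: a fraction f of the laparoscopic arm is removed and none of the open arm, and those removed have 3-year DFS d of 40-60%. The documents give no value for d. If the arm's full-set DFS is p, then

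shift = f × (p − d)/(1 − f).

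Example: 0.05 × (0.823 − 0.40)/0.95 = 0.022, or 2.2 points.

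| f | True DFS p | d = 60% | d = 40% |
|---|---|---|---|
| 5% | 82.3% | 1.2 points | 2.2 points |
| 9% | 82.3% | 2.2 points | 4.2 points |
| 5% | 72.3% | 0.6 points | 1.7 points |
| 9% | 72.3% | 1.2 points | 3.2 points |

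If d = p the shift is zero. If both arms lose similar patients in similar proportion, the difference between arms is about unchanged.

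**4. What that does to the error rate.** Further assumptions: true difference exactly −10 points, 710 and 355 randomized, no censoring, a normal approximation for the difference in 3-year rates, and nominal one-sided error 2.5%. Removing 20 of 710 laparoscopic patients (2.8%), half of them would-be events, leaves a DFS of 1 − (196.8 − 10)/690 = 72.9%. The one-sided error becomes 4.3%. If three-quarters are would-be events it is 7.5%. With 35 removed (4.9%), the figures are 6.4% and 15.2%. If removals are unrelated to outcome it stays at 2.5%.

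**The case against.** The best defence is that the plan is more transparent than the SAP sentence suggests. Eligibility is approved before randomization (protocol 9.1). SAP Table 2 lists every case outside mITT by group, centre, stage and reason, so an imbalance by arm would be visible. The plan is settled before lock, and the size calculation is a one-arm extreme. All of this is true. But a listing reports who was removed; it does not limit who may be removed, and no planned analysis puts those patients back.

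Some stronger readings are tempting, and the documents do not support them.

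- **That metastases, T4b disease or combined resection found at surgery remove patients.** "Need to remove other organs in addition to the rectum" is an eligibility criterion, and no section says that meeting it in theatre takes a patient out of the analysis. The shells suggest the opposite: SAP Table 4 has a row for "Combined resection, n" (%), and SAP Table 5 has rows for pT4b and stages IVA and IVB. Abdominal exploration is also specified in both arms.
- **That FAS is a third live population.** It appears once in the protocol, which defers details to the SAP, and the SAP line says mITT. It is a leftover label.
- **That the 97 are discretionary removals.** The allowance covers both arms and could consist wholly of patients never operated on.
- **That biased exclusions occurred or were intended.** Nothing shows or directs this.

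**Conclusion.** The point holds on the wording. The primary set is undefined in the SAP, conflicts with the protocol, and is not protected against removals made with knowledge of the arm.

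Its size is an upper illustration, not an expectation: 1.2-4.2 points on laparoscopic 3-year DFS at a true rate of 82.3%, and 0.6-3.2 points at 72.3%, against a 10-point margin. The second range is the more relevant to a false claim of noninferiority, because that error arises when the true rate lies at the margin. Both rest on removals confined to one arm and on an assumed DFS of 40-60% among those removed. The shift is about zero if removals are balanced or unrelated to outcome.

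This should be fixed because it governs who is counted in the primary comparison. Adopting the protocol's rule as it stands would cure the circularity, but it would still condition on an event after randomization.

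**What to change.** Put one definition in both documents.

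- **Set.** All randomized patients, analysed in the arm assigned.
- **Permitted removals, as a closed list.** (a) Ineligibility from facts recorded before randomization, adjudicated blind to arm and outcome. (b) Refusal of any further use of data. Report both by arm.
- **Stated non-grounds.** Patients who decline surgery or switch approach stay in. Findings at or after surgery do not remove a patient from the analysis set. Withdrawal from surgery is not a ground, because in an open-label trial it can be driven by the allocation.
- **Time origin.** Count DFS from randomization, as OS already is. Otherwise non-operated patients have no start date and cannot enter the analysis.
- **Sensitivity analysis.** Keep the protocol's operated set, with DFS from surgery.
- **Label.** Replace FAS with mITT in protocol 12.2(1).

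The cost is mainly wording, but not only that. DFS status must be collected for a few non-operated patients, and the start date of the primary endpoint changes. For stage II/III that change should be small. Preoperative examinations fall 6-7 weeks after radiotherapy (protocol 9.2) and surgery 6-8 weeks after it (protocol 6.2), which leaves at most about 8 − 6 = 2 weeks if the schedule is kept. The documents give no such interval for stage I.

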#### **8.4.6 Operative outcomes**

- **Conversion to Open Surgery**

The conversion is defined as any part of the mesorectal dissection using the traditional open surgery. The surgeon decided on the conversion after considering patient safety, technical difficulties, and relevant conditions influencing the completion of TME.

- **Operative time**

Operative time is defined as the time from skin incision to the completion of skin suture.

- **Estimated blood loss**

Estimated blood loss will be measured according to the suction and the weight of wet gauze, and then minus the irrigation.

- **Intraoperative outcomes**

Intraoperative outcomes are defined as events occurring during surgery and details of the surgical procedure, such as conversion, operative time, estimated blood loss, type of surgery, and diverting ostomy creation.

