#### **● Per-protocol set (PPS):**

The PPS includes patients who meet the inclusion criteria, do not meet the exclusion criteria, and complete the treatment plan. In other words, the participants who meet the trial plan, have good compliance, and complete the items specified in the eCRF are included in the per-protocol (PP) analysis. PP analysis is mainly applied to the primary outcome measure.

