#### ■ 30-day postoperative complications

#### ■ 30-day postoperative mortality

#### ■ 3-year and 5-year OS rates (calculated 3 and 5 years after the last participant is enrolled)

#### ■ Locoregional recurrence rate

### **7.3 Other pre-specified outcome measures**

#### ■ Operative outcomes:

1) Operation time (min)

2) Estimated blood loss (ml)

3) Conversion to open surgery (only applicable to the laparoscopic resection group)

4) Events of intraoperative complications

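### The per-protocol set is defined differently in protocol and SAP, and both definitions set conditions that an early relapse or death can break

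*Combined protocol and SAP*

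**What the plan says.** The two definitions start differently.

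- Protocol 12.1: "The PPS includes patients who meet the inclusion criteria, do not meet the exclusion criteria, and complete the treatment plan". It does not mention the assigned operation.
- SAP 8.2: "The PPS includes patients who underwent the assigned surgery only". It does not mention finishing treatment.

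Each then offers a restatement that is really a further set of conditions. In the SAP, "the participants who meet the trial plan, have good compliance, and complete the items specified in the eCRF are included" in the analysis; the protocol is to the same effect. Neither gives a threshold for compliance, nor an exception for items left undone because the patient relapsed or died.

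The set has one main use: "PP analysis is mainly applied to the primary outcome measure". SAP section 9 gives it its own DFS table (Table 8) and Kaplan-Meier figure (Figure 2). It is not the primary population: "The modified intention-to-treat (mITT) population will serve as the primary population for efficacy analyses in this study". Neither document says how an mITT result and a per-protocol result that disagree would be read together.

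On conversion, protocol 8.4.6 says: "The conversion is defined as any part of the mesorectal dissection using the traditional open surgery". The surgeon decides on it for safety or technical reasons. Protocol 8.3 and SAP 7.3 list it as an outcome of the laparoscopic group alone. Neither document says whether a converted patient belongs to the per-protocol set.

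**The concern.** A per-protocol analysis in a noninferiority trial is usually read as a second look at the main result, less diluted by departures from the assigned treatment. That works only if membership does not depend on the outcome.

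Here it can. DFS runs from surgery to recurrence or death (protocol 8.4.1). Protocol 9.8.1 continues chemotherapy after surgery for patients who had preoperative chemoradiotherapy, and Appendix 2 schedules questionnaires at 3, 6 and 12 months and tumor assessments to month 60. A patient who dies at month 4 can finish neither the treatment plan nor the later items. Taken at their word, the conditions remove that patient because of the endpoint.

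The SAP's assigned-surgery condition raises a second issue. If conversions count as not having had the assigned operation, a filter applied after randomization acts on one arm only, on cases selected for difficulty.

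The trial is open-label, and protocol section 12 lets the analysis plan be finalized before database lock in light of the data. Unclear membership could then be settled with arm and outcome known.

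**Working it through.** **The plan's own figure.** From SAP 8.1: open-arm 3-year DFS 94.3% (stage I) and 75.2% (stage II/III), margin 10 points, one-sided alpha 2.5%, power 80%, allocation about 2:1, dropout 20%. I read the stated periods as 3 years' accrual and 5 years' follow-up, and assume exponential DFS and a true hazard ratio of 1.

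The margin hazard ratio is h = ln(p − 0.10)/ln(p). With a = 2/3 and b = 1/3, the events needed are [(1.96·s0 + 0.84·s1)/m]², where m = ah/(ah + b) − a, s0 = √(abh)/(ah + b) and s1 = √(ab).

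- Stage I: h = 2.910; 34.1 events; event probability 0.1193; N = 285.8; 285.8/0.8 = 357.2 (stated 359).
- Stage II/III: h = 1.501; 222.9 events; event probability 0.4589; N = 485.7; 485.7/0.8 = 607.1 (stated 609).

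The total is 964 against the stated 968, so the figure reproduces to 0.4%. It does not depend on the per-protocol definition.

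**Illustration of the bias.** Take stage II/III with 406 laparoscopic and 203 open patients and a true deficit equal to the margin: open 0.752, laparoscopic 0.652. The test compares 3-year proportions with unpooled variance at one-sided 2.5%. This simplifies the planned Cox analysis. The chance of declaring noninferiority is Φ[(difference + 0.10)/SE − 1.96], which is 2.5% with no exclusions. All exclusion rates below are assumptions.

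*Failures removed.* If a share f of an arm's failures is dropped, its DFS becomes p/(1 − f(1 − p)) and its size n(1 − f(1 − p)).

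| Failures dropped: laparoscopic / open | Laparoscopic DFS | Open DFS | Difference | False noninferiority |
|---|---|---|---|---|
| 10% / 10% | 0.6755 | 0.7711 | −0.0956 | 3.3% |
| 20% / 20% | 0.7008 | 0.7912 | −0.0905 | 4.4% |
| 10% / 20% | 0.6755 | 0.7912 | −0.1157 | 0.9% |
| 20% / 10% | 0.7008 | 0.7711 | −0.0704 | 11.9% |

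For the first row, SE = √(0.6755·0.3245/391.9 + 0.7711·0.2289/198.0) = 0.0381, and Φ(0.0044/0.0381 − 1.96) ≈ 0.033.

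Even an equal loss has to be defined. If failures amounting to the same 5% of all patients are dropped from each arm, the proportions become 0.652/0.95 = 0.686 and 0.752/0.95 = 0.792. The difference widens to −0.105 and the rate falls to Φ(−0.0053/0.0376 − 1.96) ≈ 1.8%.

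*Conversions removed.* If a share c converts and has DFS lower by g than other laparoscopic patients, dropping them raises laparoscopic DFS by c·g.

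| Conversion rate | g = −10 points (converted do better) | g = 0 | g = 10 points | g = 20 points |
|---|---|---|---|---|
| 2% | 2.2% | 2.5% | 2.8% | 3.2% |
| 5% | 1.8% | 2.5% | 3.4% | 4.4% |
| 10% | 1.3% | 2.5% | 4.4% | 7.4% |

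For 10% and 20 points, the shift is 0.10 × 0.20 = 2.0 points, one fifth of the margin.

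**The case against.** The strongest reply is that the documents nowhere say that conversions or early failures are excluded. Conversion is a permitted surgical decision. The SAP's assigned-surgery condition may be aimed at crossovers only, with a laparoscopic start later converted still counting as assigned treatment. Under the protocol's definition, conversion breaches nothing stated. This stands: a reader might infer that conversions are dropped, and the SAP wording allows it, but it is not a written rule.

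On early failures, protocol 17.2 has missed examinations recorded in the eCRF, so an early event need not leave the form incomplete. Stage I patients not upstaged at pathology have no planned chemotherapy to finish, and stage I is 359 of the 968 planned. Both points narrow the problem. Neither removes the compliance condition or, for stage II/III patients under the protocol, the requirement to finish treatment.

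The reply is also right that the size rests on assumptions. Protocol 18.2 requires experienced, accredited surgeons, which argues against a high conversion rate. The planned tables show set sizes by arm, conversions, and mITT and per-protocol DFS separately, and exclusions are to be listed with reasons, so some of the selection would be visible.

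**Conclusion.** The point holds as a defect of definition. The two documents define the set differently, both admit patients on conditions that the endpoint itself can break, and neither classifies conversions. The per-protocol DFS result may be biased, plausibly toward noninferiority. In the stage II/III illustration the false noninferiority rate is 3.3% to 4.4%, against 2.5%, if the same 10% to 20% share of failures is dropped from each arm. It is 0.9% to 11.9% if the arms lose unequal shares, and 1.3% to 7.4% if conversions are dropped.

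A reader might go further and infer that the set is biased toward noninferiority and useless as a check. The documents do not support that. They give no conversion rate, no prognosis for converted patients and no exclusion rates, and the sign changes with those inputs. Nor do they make the per-protocol result a condition for concluding noninferiority. The mITT analysis is primary and is untouched by this.

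**What to change.** Use one per-protocol definition, word for word, in protocol 12.1 and SAP 8.2. Base it on eligibility judged from pre-randomization data and on the surgical approach received or begun.

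Delete three membership conditions: finishing the treatment plan, good compliance, and completing the eCRF items. Censor incomplete follow-up instead, so that nobody leaves the set because of recurrence or death.

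State how conversions are classified. One option is to keep them in the laparoscopic arm because the operation began by the assigned approach. Report the other classification as a sensitivity analysis. The choice is open to argument; what matters is that it is fixed in advance.

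The cost is wording in two documents. No new data are needed, since conversion is already recorded. The downside is that the per-protocol set moves closer to the mITT set and adds less as a separate analysis.
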